### Population size

The sample size needed to show a statistically significant difference between treatment depends on the proportion of patients successfully weaned and the proportion succumbing to a competing risk prior to successful weaning by day 30 (see the previous section “Outcomes”). Since TTVDP is a novel, first-of-its-kind therapy both in general and in the population of patients experiencing difficult weaning from MV, no estimates of the effect size or the competing events were available. Consequently, a sample of convenience was used to allow enrollment and randomization of up to 88 study patients (44 per arm).

Using a competing risks model with a log rank test (PASS 14, NCSS Statistical Software, LLC, Kaysville, UT, USA), this population size gives the study a 70% power to find a statistically significant difference in the event of a dramatically large treatment effect (i.e., approximately 50% of patients weaned with 34% experiencing one of the competing risks in the control group, vs. 80% weaned with 11% experiencing one of the competing risks in the TTVDP group).

As a result, the totality of evidence is expected to indicate a trend in favor of TTVDP (with an adverse event profile not significantly different between the groups) rather than to show definitive superiority.

Of note, Revision F of the protocol as described in this manuscript is being amended to account for a higher than expected number of withdrawals due to inability to insert the guidewire: the target size population will be brought from 88 to 110, with the possibility for sites to include two roll-in subjects for training purposes. Accordingly, the number of participating centers will be increased from 14 to 22.

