Regarding the primary efficacy endpoint (time to successful extubation without reintubation in the next 48 h), the null hypothesis states the cumulative incidence by day 30 for successful weaning is the same in patients randomized to treatment or control groups. The primary statistical analysis will be conducted on the mITT population and will model the time to the event of interest in the presence of competing events which include death and withdrawal of life support. In addition, cessation of weaning in the ICU with discharge from ICU to a specialized weaning facility will be evaluated. Patients who do not meet one of the endpoints by the end of their study follow-up will be censored at the time of study discontinuation or completion. The primary statistical model will utilize the cumulative incidence function. The event of interest, successful weaning, will be compared between randomized groups using Gray’s test. The probabilities will be summarized for successful weaning and each competing event for the duration of the study. The 95% confidence intervals will be provided for the probabilities at 30 days. In addition, descriptive statistics will be prepared by randomized group for the time to successful weaning in days.

All ITT patients will be included in the primary safety endpoint analysis. Fisher’s exact test will be used to compare the number of patients with an event or in a category of events out of the total number of patients randomized between groups as a tool to understand the adverse event profile associated with TTVDP compared to control.

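### The stated 70% power belongs to a cause-specific log-rank test on all 44 + 44 patients, whereas the primary analysis is Gray's test on the mITT set, for which 70% understates power in the stated scenario

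*Protocol article*

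**What the plan says.** Under Population size, the article explains that no estimates of effect or of competing events were available, so that "a sample of convenience was used to allow enrollment and randomization of up to 88 study patients (44 per arm") . It then gives a power figure, obtained "Using a competing risks model with a log rank test (PASS 14"), and states that "this population size gives the study a 70% power to find a statistically significant difference in the event of a dramatically large treatment effect". The scenario is "approximately 50% of patients weaned with 34% experiencing one of the competing risks in the control group", against "80% weaned with 11% experiencing one of the competing risks in the TTVDP group". The next paragraph presents the expectation of a trend, and not of definitive superiority, as following from this.

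Under Statistical analysis, the null hypothesis is equal cumulative incidence of weaning by day 30. The test is named in the sentence beginning "The event of interest, successful weaning, will be compared between randomized groups using Gray", that is, Gray's test. The set is also fixed: "The primary statistical analysis will be conducted on the mITT population". The mITT set is defined as every control plus those TTVDP patients whose left subclavian vein was successfully cannulated. The significance level is two-sided 0.05.

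Population size also reports more withdrawals than expected because the guidewire could not be inserted, and announces a rise from 88 to 110. Trial status adds that Revision K will follow patients transferred to an outside facility and take that event off the list of competing risks.

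**The concern.** A power statement should describe the test and the patients of the primary analysis. Here both differ. A log-rank test that censors competing events compares cause-specific hazards of weaning. Gray's test compares cumulative incidence, which also responds to how many patients die or otherwise leave the risk set through a competing event. When one arm is assumed to have 34% competing events and the other 11%, the two tests face different effect sizes, so the power of one cannot stand in for that of the other. The article names no log-rank analysis of the weaning endpoint.

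Two things are at stake. The figure is the stated ground for what the trial is expected to show, so it affects how a null or borderline result will be read. It also cannot be carried forward to 110 patients, because it describes another test and another analysis set.

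**Working it through.** **Inputs.** From Population size: 44 per arm; control 50% weaned and 34% competing by day 30; TTVDP 80% and 11%. From Statistical analysis: two-sided 0.05, Gray's test, mITT. Assumed here: constant hazards, no random censoring before day 30, and unchanged rates among cannulated patients. The cannulation-failure rate is not in the article; a range of 10–30% of the TTVDP arm is assumed.

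**Step 1: reproduce the 70%.** With constant hazards, the cause-specific weaning hazard over 30 days is F_wean × (−ln(1 − F_wean − F_comp)) / (F_wean + F_comp).

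- Control: 0.50 × (−ln 0.16) / 0.84 = 1.091, or 0.0364 per day.
- TTVDP: 0.80 × (−ln 0.09) / 0.91 = 2.117, or 0.0706 per day.
- Hazard ratio: 2.117 / 1.091 = 1.94.
- Expected weaning events: 44 × 0.50 + 44 × 0.80 = 57.2.
- Power: Φ(√57.2 / 2 × ln 1.94 − 1.96) = Φ(0.547) = 70.8%.

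Simulation of the cause-specific log-rank test (10,000 runs) gives 69.9%. A one-sided version gives 80.6%, which does not match. The article does not use the term cause-specific; the reproduction identifies the test.

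**Step 2: Gray's test, same scenario, 44/44.** The ratio of subdistribution hazards implied by the day-30 incidences is ln(1 − 0.80) / ln(1 − 0.50) = 2.32. The formula gives Φ(√57.2 / 2 × ln 2.32 − 1.96) = Φ(1.226) = 89.0%. Simulation, with competing events kept at risk to day 30, gives 86.5% (type I error 4.7%). The simulated value is preferred, because constant cause-specific hazards do not give proportional subdistribution hazards.

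**Step 3: Gray's test on mITT, same scenario.** Only the TTVDP arm shrinks.

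| Assumed TTVDP loss | Controls / TTVDP | Gray's test (simulated) | Cause-specific log-rank (simulated) |
|---|---|---|---|
| 0% | 44 / 44 | 86.5% | 69.9% |
| 10% | 44 / 40 | 84.5% | 66.6% |
| 20% | 44 / 35 | 82.2% | 65.5% |
| 30% | 44 / 31 | 80.0% | 63.1% |

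The two mismatches act in opposite directions. In simulation the change of test adds about 17 points (86.5 − 69.9), and the loss of TTVDP patients removes about 2 to 7 (86.5 − 84.5 to 86.5 − 80.0).

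**Step 4: how far this rests on fewer competing events.** Keep the TTVDP weaning hazard at 0.0706 per day, but set its competing hazard to the control value, 0.34 × (−ln 0.16) / 0.84 / 30 = 0.0247 per day. The total is 0.0953, so TTVDP weaning by day 30 is 0.0706 / 0.0953 × (1 − exp(−30 × 0.0953)) = 0.698, against 0.50 in controls. Simulated power of Gray's test is then about 55% with 44/44 and about 51% with 44/35.

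**The case against.** The 70% contains no error of arithmetic: the article names the test, the software and all four rates, and the number follows from them. It also sets nothing, because 88 is openly a sample of convenience and the Discussion calls that a limitation. In the stated scenario the discrepancy is on the safe side. The competing-event rates are printed beside the figure, so the assumption is disclosed. The rise to 110 is meant to offset failed insertions: at an assumed 20% loss, 55 per arm leaves 44 treated. Revision K is not shown, so the lack of a restated power for 110 cannot be held against a condensed article.

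Most of this stands, and it limits the weight of the point. It does not remove the mismatch: the article states both a power and a primary analysis, and the one is not the power of the other. Disclosing 34% and 11% does not tell a reader that the planned test gains from that difference while the test behind the 70% largely does not.

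Two stronger readings are tempting. A reader might infer that power is overstated because mITT loses patients. The documents do not support this in the stated scenario, where Gray's test stays at about 80% or more across the assumed range of loss. A reader might also infer that expecting only a trend is now wrong. That does not follow either: the scenario is described as dramatically large, and for a smaller effect (assumed 65% weaned, 24% competing in the TTVDP arm) Gray's test has only about 30% power with 44/44.

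**Conclusion.** The point holds as a mismatch between the planning figure and the planned analysis. The 70% is right for a two-sided cause-specific log-rank test on all 44 + 44 patients and for nothing else planned here. In the article's own scenario Gray's test has about 86% power with 44/44 and about 80–84% on mITT, so 70% understates it. If TTVDP speeds weaning as assumed but leaves the competing hazard alone, power is about 55% (44/44) or 51% (44/35).

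These results rest on constant hazards, no random censoring, unchanged rates among cannulated patients, and an assumed loss of 10–30%. They apply to 88 patients under Revision F. They should not be carried to 110 with the same 34% and 11%, because Revision K changes which events compete. The consequence is for interpretation, not for the design.

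**What to change.** Replace the sentence giving 70% with the power of Gray's test on the mITT set at 88 patients. Show it for two scenarios: the one stated, and one with the competing hazard unchanged from control. Give the cannulation-failure rate as an assumption with a range. For 110 patients, recompute with rates that match Revision K's definition of competing events.

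The expectation of a trend may stay, but it should rest on the convenience sample and on how large or optimistic the assumed effect is, not on the 70%. If the log-rank figure is kept for the record, label it as cause-specific and as assuming that all 88 are analysed.

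The cost is one recalculation and a few reworded sentences. The sample size, test and analysis set need not change.

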### Statistical analysis

After the database is audited and locked, the statistical analysis will be conducted by a statistician independent of the sponsor and the CRO. The statistical plan described in the study protocol includes details about handling missing data, assessing comparability of randomized groups, and evaluating the pooled data collected at the various centers.

The data from the study will only be analyzed once at the end of the study, and no formal statistical stopping rules allow for the early termination of this study.

The analysis groups include the (1) intent-to-treat (ITT) population, defined as all patients who were randomized with a study group defined by the randomization; (2) modified intent-to-treat (mITT) population, defined as the complete control group and a subset of the ITT therapy group with successful cannulation of the left subclavian vein; and (3) per protocol (PP) population, i.e., a subset of the mITT population defined as those patients who completed at least 75% of the protocol-required stimulations in at least one phrenic nerve. The sidedness of the phrenic nerve stimulation can change from left to right or can occur in both phrenic nerves.

Descriptive statistics for continuous variables will include the number of observations, mean, standard deviation, minimum, median, and maximum. Descriptive statistics for categorical variables will include the number and percent in each category out of the total number of observed responses. The *p* values will be considered statistically significant if the two-sided *p* value is ≤0.05 unless otherwise specified. When the arithmetic mean is found not to be an appropriate measure of central tendency, alternative statistics will be considered (e.g., median, interquartile range). When the distribution of a variable does not support the use of parametric statistics, nonparametric approaches or data transformations may be implemented. If data transformations are used, they will be specified in the final clinical study report.

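### A non-significant adverse event comparison is the expected favourable safety reading, but at 44 per arm it cannot support comparable safety

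*Protocol article*

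**What the plan says.** The Protocol article, section Population size, explains that no effect-size estimates existed and that "a sample of convenience was used to allow enrollment and randomization of up to 88 study patients (44 per arm"). It quotes 70% power for a very large efficacy effect. It then says that, as a result, the overall evidence is expected to point to a trend for TTVDP, "with an adverse event profile not significantly different between the groups) rather than to show definitive superiority". The same section announces that "the target size population will be brought from 88 to 110".

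The section Statistical analysis gives the safety comparison: "All ITT patients will be included in the primary safety endpoint analysis", and Fisher's "exact test will be used to compare the number of patients with an event or in a category of events". The test is described "as a tool to understand the adverse event profile associated with TTVDP compared to control". The general rule in that section is that p "values will be considered statistically significant if the two-sided" p "value is ≤0.05 unless otherwise specified".

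The only power figure in the article is for efficacy. For the primary endpoint, Statistical analysis promises 95% confidence intervals for the day-30 probabilities. For safety, it names the test alone.

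**The concern.** One sentence applies two standards. Efficacy may count in the device's favour on a trend that falls short of significance, while harm is read favourably so long as it does not reach significance. The small sample that excuses the first also makes the second easy to meet. A non-significant p-value from a small comparison does not show that two arms are alike, and it does not tell the reader how large an excess remains possible.

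This matters because evaluating safety is a stated aim (Abstract and Background) and the device is invasive. Under Risk-benefit balance, the article itself calls the risks of pacing less well defined than those of subclavian catheterization. If the report follows the sentence in Population size, readers may take a non-significant Fisher test as reassurance that the data cannot give.

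**Working it through.** **The plan's own figure (efficacy).** The inputs from Population size are 44 per arm, control 50% weaned and 34% competing events, TTVDP 80% weaned and 11% competing events. Constant cause-specific hazards are assumed.

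- Control weaning hazard: −ln(1 − 0.84) × 50/84 = 1.091. TTVDP: −ln(1 − 0.91) × 80/91 = 2.117. Hazard ratio = 1.941.
- Weaning events: 44 × 0.50 + 44 × 0.80 = 57.2.
- Schoenfeld power, two-sided 0.05: Φ(√(57.2/4) × ln 1.941 − 1.96) = 70.8%.

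This agrees with the stated 70%, which is not in dispute. It says nothing about safety, and no safety figure exists to reproduce.

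**Inputs for the safety check.** 44 per arm (Population size); two-sided Fisher's exact test on patients with an event, significance at p ≤ 0.05, all randomized patients (Statistical analysis). The amended target of 110 gives 55 per arm if 1:1 allocation is kept.

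**Where the threshold lies with no control events.** With k events in TTVDP and none in control, the one-sided Fisher p is C(44, k)/C(88, k). With equal arms the two-sided p is twice that.

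- k = 5: 2 × 1,086,008/39,175,752 = 0.0554.
- k = 6: 2 × 7,059,052/541,931,236 = 0.0261.

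| TTVDP vs control events | p, 44 per arm | p, 55 per arm |
|---|---|---|
| 3 vs 0 | 0.241 | 0.243 |
| 4 vs 0 | 0.116 | 0.118 |
| 5 vs 0 | 0.055 | 0.057 |
| 6 vs 0 | 0.026 | 0.027 |

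Six against none is the smallest significant split at either size. Against 1, 2, 3 or 4 control events, significance at 44 per arm needs 8, 9, 11 or 13 TTVDP events.

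**What 5/44 vs 0/44 leaves open.** The observed excess is 5/44 = 11.4 percentage points. The Wilson 95% limits are 0.0495 to 0.2398 for 5/44 and 0 to 0.0803 for 0/44. Newcombe's interval for the difference is:

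- lower: 0.1136 − √[(0.1136 − 0.0495)² + 0.0803²] = 0.011;
- upper: 0.1136 + √[(0.2398 − 0.1136)² + 0²] = 0.240.

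The interval is about 1 to 24 points. The result would be reported as non-significant although the interval lies above zero and reaches nearly one patient in four.

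**Power for an event specific to the study device.** The control rate is taken as 0%. The TTVDP rates are assumptions, because the article gives no adverse event rates. Power is P(X ≥ 6) with X binomial.

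| True TTVDP rate | 44 per arm | 55 per arm |
|---|---|---|
| 5% | 2% | 6% |
| 10% | 27% | 48% |
| 15% | 66% | 85% |
| 20% | 90% | 98% |

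**Power for events that controls can also have.** By exact enumeration at 44 per arm, again with assumed rates (control vs TTVDP): 5% vs 15% gives 22%, 10% vs 20% gives 17%, 10% vs 25% gives 35%, and 10% vs 30% gives 56%.

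**The case against.** The strongest reply is that the sentence is a parenthesis about what the evidence is expected to show, in a section that openly admits a sample of convenience. Nothing in the article says that safety will be concluded from p > 0.05, and Statistical analysis already gives Fisher's test a descriptive role. This stands. A reader might infer a formal safety criterion that the device passes by non-significance, but the text does not support that.

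Safety judgement also does not rest on Fisher's test alone. Under Safety, investigators assess each event for severity and for its relationship to the device or procedure, and serious events go to the sponsor within 24 h and on to the authorities. Under Monitoring, an independent Clinical Events Committee adjudicates serious events, and a Data and Safety Monitoring Board may recommend stopping. Five device-related events against none would be visible whatever the p-value. This stands too, so it would be wrong to infer that such harms would go unnoticed. These safeguards do not, however, change how the between-group comparison is read in the report.

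A reader might also infer that controls never have a central line. Study setting says that they do not receive the study catheter. Under Masking in the Discussion, a central line remains possible for a control patient if the treating clinicians decide on one. A zero control rate is therefore secure only for events specific to the study device.

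The 5 vs 0 split is the largest non-significant one with no control events, so it is a boundary case. It marks the threshold, and the power figures do not depend on it. They also show that large device-specific excesses, near 20%, would probably be detected.

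Finally, the full protocol or analysis plan may specify confidence intervals for adverse events. Their absence from a condensed article is not the point. The point is the sentence that is printed.

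**Conclusion.** The point holds as a matter of interpretation. The article offers a non-significant adverse event comparison as the favourable safety reading at a size where non-significance is compatible with a substantial excess: 5/44 vs 0/44 gives p = 0.055 with an interval of about 1 to 24 points. For a device-specific event, power is 2% at a true rate of 5% and 27% at 10%, rising to 66% at 15% and 90% at 20%. Going to 110 patients raises power but leaves the threshold at six events against none.

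The p-values and the interval use only the article's sample size, test and significance level. The power figures rest on assumed event rates and, in the device-specific case, on a control rate of zero. No endpoint, test or analysis population needs to change.

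**What to change.** In Population size, remove the expectation that the adverse event profile will not differ significantly. In the analysis plan and report:

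- give the risk difference (TTVDP minus control) with its 95% confidence interval for serious adverse events, device- or procedure-related events, deaths and the main adverse event categories;
- keep Fisher p-values as descriptive information;
- state that p > 0.05 will not be read as comparable safety.

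The cost is a change of wording and one extra column per safety table, with no change to design, conduct or data collection. The drawback for the sponsor is a less favourable safety statement, because the upper confidence limits will show how much excess harm remains possible.

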### Data processing

#### Procedures

The RESCUE 2 study complies with the Declaration of Helsinki and will be conducted in accordance with the principles of Good Clinical Practice. Standardized procedures and specific training will be required as investigators select participants, obtain informed consent, and perform protocol-specific actions and measurements, including, for example, VLTs, MIP measurements, diaphragmatic ultrasound imaging, adverse event reporting, data recording, and statistical analyses.

#### Data management

Data management will be assigned to a dedicated contract research organization (CRO), namely Syntactx Ltd., Brussels, Belgium. The Syncrony™ web-based EDC database manufactured by Syntactx Technologies (New York, NY, USA) is being used to record and manage study data and to provide an audit trail. The electronic clinical data system was validated prior to first use in accordance with the CRO’s standard operating procedures. Electronic case report form (eCRF) completion guidelines and instructions for electronic data entry were developed in conjunction with the sponsor and the CRO. The EDC data can be exported to various file formats for statistical analysis. Patient data are fully anonymized, and all study numbers to identify study patients are stored separately and securely with limited access by the researchers and monitors. All data queries will be resolved before the database is locked for analysis at the end of the trial.

### Safety

Extensive preclinical testing of the LIVE® Catheter system has been conducted in compliance with harmonized standards and international medical device directives. Prior to human testing, bench and animal testing ensured that the device met the minimum design requirements for various measures, including (but not limited to) system integrity, biocompatibility, sterility, and packaging/storage integrity. The safety of the system was initially tested in a first-in-human study [30], and this RESCUE 2 study will optimize the risk/benefit balance by (1) excluding patients with conditions thought to increase procedural risks or to decrease the probability of efficacy; (2) selecting experienced investigators and experienced clinical research teams; (3) training investigators on the protocol implementation methods; and (4) utilizing experienced medical professionals to continuously monitor study patients during the catheter placement procedures and during therapy sessions.

The principal investigator at each participating center is responsible for overseeing the timely and adequate reporting of adverse events, adverse device effects, and device deficiencies, per the corresponding definitions provided in the study protocol. Investigators will report SAEs and serious adverse device effects to the study sponsor within 24 h of their first knowledge of the event. Each reported adverse event will be qualified as anticipated (a list of anticipated events exists in the study protocol) or unanticipated. The event will be assessed by the investigator for its relationship to the device or procedure (not related, unknown, possible, probable, definite) and for its severity. Adverse events will be reported on the eCRF as soon as practically possible. In case of death, the relationship of death to the medical device and/or the study will be documented as precisely as possible. The study is overseen by a Clinical Events Committee as well as a Data and Safety Monitoring Board.

The study sponsor will report SAEs, serious adverse device effects, and device deficiencies that might have led to an SAE to the national competent authorities of each country where the study is taking place.

